### Randomisation and blinding

The first participant recruited to the trial will be randomised to either the adaptive or non-adaptive CCT group. The following participants will then be allocated to either group using minimization [31]. Participant group allocation details will be documented and stored securely by the chief investigator in a password-protected file. As a single-blind trial, participants will be blind to group allocation and it will not be possible for participants to tell from the online CCT interface which group they have been assigned to.

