## Methods/design

A single-blind, head-to-head, randomised controlled trial (RCT) design will be used to determine whether auditory training combined with adaptive CCT will elicit greater improvement in study outcomes in adult cochlear implant recipients, when compared to auditory training combined with non-adaptive (i.e. placebo) CCT (see Fig. 1). Following enrolment into the study, participants will complete a pre-intervention assessment (*T*_0_) of speech/sound perception, cognition, mood, and quality of life, followed by their cochlear implant surgery and randomisation to either the intervention group (auditory training + adaptive CCT) or the control group (auditory training + non-adaptive CCT). Participants will then complete the 12-week training intervention followed by a post-intervention assessment (*T*_1_) and 3-month follow-up assessment (*T*_2_) involving the same outcomes measured at pre-intervention. Previous cognitive training studies have used a training period of 4–8 weeks [17]. For the current study, a training intervention of 12 weeks has been chosen to ensure participants gain the full benefits of the training. A follow-up at 3 months has been deemed appropriate to ensure continued participant interest and prevent high attrition rates. The use of an active control group will ensure that participants are blind to whether they are receiving adaptive or non-adaptive training, which helps eliminate potential placebo effects of training. The RCT will be conducted at Ear Science Institute Australia, Perth, Western Australia. Ethics approval for the study was received from the University of Western Australia Human Research Ethics Committee (RA/4/20/5287), and the trial was registered with the Australian and New Zealand Clinical Trials Registry (ACTRN12619000609156).

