### Test procedure

Participants who meet the clinical criteria for a cochlear implant will be recruited into the study. Participants will complete audiometric testing and speech/sound perception assessment within the 12 months preceding surgery and complete the pre-intervention cognitive, mood, and quality of life assessment within 1 week prior to implant. Participants will have the option to complete the pre-intervention assessment in their home or at the Ear Science Institute Australia at a time that is most convenient to them. Following cochlear implant surgery and recovery, participants will attend their ‘switch-on’ appointment where they will be provided with the standardised auditory training material by their implant audiologist. Following ‘switch-on’ appointments, participants will be randomised to either the adaptive or non-adaptive CCT group and the lead researcher will schedule a time within the same week to visit participant homes to set up the CCT equipment. As the CCT platform, Brain HQ will be delivered via the internet to participant’s home computers and the lead researcher will spend time explaining and demonstrating how to use the platform. Participant adherence to the training will be automatically monitored by the program and remotely by the lead researcher. Participants will be sent regular text messages during the intervention as polite reminders to complete their CCT sessions. Following completion of the training, participants will complete audiometric testing and a post-intervention assessment of their speech/sound perception, cognition, mood, and quality of life. The same outcomes will also be measured at the 3-month follow-up assessment to provide evidence of long-term benefits of CCT.

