### Power analysis and sample size

Evidence from our recent meta-analysis of cognitive training for adults with hearing loss reported beneficial effects ranging from small to large [17], with contributing studies including 10 to 67 participants. Using G*Power (34), an a priori power analysis was conducted to determine the required sample size when comparing two intervention groups across three measurement intervals (i.e. pre-intervention, post-intervention, and 3-month follow-up) for any of the primary outcome measures (speech/sound perception or cognition). To detect a medium effect (*f*
^2^ = .25) at an alpha of .05 and power of .90, 36 participants will need to be recruited. To account for potential 20% attrition, 44 participants (i.e. 22 per group) will be targeted for recruitment.

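### As written, only the first of 44 participants is randomised and no random element is stated for the minimisation of the other 43, so many allocations may be predictable to unblinded site staff

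*Protocol article*

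**What the plan says.** The Randomisation and blinding section of the protocol article gives the allocation rule in two steps. For the first person: "The first participant recruited to the trial will be randomised to either the adaptive or non-adaptive CCT group". For everyone else: "The following participants will then be allocated to either group using minimization", with a literature reference. It states no allocation probability below 1, no rule for ties and no independent operator.

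The Test procedure section describes allocation differently. After switch-on, "participants will be randomised to either the adaptive or non-adaptive CCT group", with no distinction between the first participant and the rest. The Abstract and Methods/design call the study a randomised controlled trial.

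Four other statements bear on who could foresee an allocation:

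- Site (Methods/design): "The RCT will be conducted at Ear Science Institute Australia, Perth, Western Australia".
- Blinding (Randomisation and blinding): "As a single-blind trial, participants will be blind to group allocation". No one else is said to be blind.
- Custody (same section): "Participant group allocation details will be documented and stored securely by the chief investigator in a password-protected file".
- Contact with the allocated arm (Test procedure): "the lead researcher will schedule a time within the same week to visit participant homes to set up the CCT equipment". The same person demonstrates the platform and monitors adherence remotely.

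The target is in Power analysis and sample size: "To account for potential 20% attrition, 44 participants (i.e. 22 per group) will be targeted for recruitment".

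**The concern.** The section says where chance enters, at the first participant, and contrasts that with the method used for the rest. Taken at its word, this is classical deterministic minimisation: once the first arm is drawn, each later participant goes to whichever arm reduces the imbalance, and chance can return only at a tie. That sits poorly with the statement in Test procedure that participants are randomised.

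Deterministic minimisation is safest when nobody in contact with participants can reconstruct the tally. Here there is one site, staff are not said to be blind, and the person who sets up the training at home very plausibly learns each arm. Someone in that position who also knows the factors could often work out the next assignment. They could then influence, even unintentionally, who is put forward next, when, or whether a hesitant participant is retained. Any such influence would undermine the comparability of the groups, and it could not be detected or corrected in the analysis.

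**Working it through.** **The plan's own figures.** The target is 44, or 2 × 22. One participant is randomised, so 44 − 1 = 43 are minimised, and 43/44 = 97.7%. The article gives no figure for predictability, so there is none to reproduce, and the sample size is not in dispute here.

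**Assumptions, because the article does not give them.** One to four independent factors with equally frequent levels, equal weights, and ties broken at random. Random tie-breaking is the generous assumption, since the article does not state it.

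**Rule simulated.** For each new participant, take the difference between arms in the number already allocated at that participant's level of each factor, and sum over factors. If the sum is not zero, assign the arm that reduces it with probability *p*. If it is zero, toss a fair coin. As written, *p* = 1. An allocation is forced when *p* = 1 and there is no tie.

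An observer who knows the factors and all past allocations guesses correctly with probability *p* × (share not tied) + 0.5 × (share tied). For three binary factors:

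- *p* = 1: 0.799 + 0.5 × 0.201 = 0.90
- *p* = 0.8, where 0.859 are not tied: 0.8 × 0.859 + 0.5 × 0.141 = 0.76

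**Results** (N = 44, allocations 2 to 44, 1,500 runs per scenario):

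| Assumed factors | Forced, *p* = 1 | Correct guess, *p* = 1 | Correct guess, *p* = 0.8 | Mean final imbalance, *p* = 1 → 0.8 |
|---|---|---|---|---|
| One binary | 50% | 75% | 69% | 0.45 → 1.13 |
| Two binary | 73% | 87% | 74% | 0.31 → 0.96 |
| Three binary | 80% | 90% | 76% | 0.28 → 0.98 |
| Four (two binary, two three-level) | 84% | 92% | 77% | 0.43 → 1.07 |

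Simple randomisation gives 50% correct guesses. Knowing only the running group totals, and not the factors, still gives 69–72% at *p* = 1.

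**Sensitivity to the scoring rule and denominator.** With the sum-of-ranges score, the forced share of allocations 2 to 44 is 50%, 73%, 78% and 82% for one to four binary factors. Counted over all 44 participants, it is 49%, 71% and 76% for one to three. This is why the shares are given as ranges: 71–73% for two factors, 76–80% for three and 82–84% for four.

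**When a prediction could be used.** Methods/design and Test procedure give the same order: enrolment, baseline assessment, surgery, switch-on, allocation, then home set-up within the same week. Cognition, mood and quality of life are measured within a week before implantation, and speech testing may be up to 12 months before surgery. To predict an arm at consent or baseline, staff would need the tally as it will stand after everyone ahead in the queue has been switched on. Close to switch-on, the current tally is enough.

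**The case against.** The strongest reply is that the article gives one sentence and a citation. The cited method or the full protocol may include a random component, and a condensed article may leave the factors, tie rule and operator to that document. This stands in part. That no random element exists is an inference from silence, and the missing factor list is not a fault in itself. But the sentence is more than silent: it assigns randomisation to the first participant and a different method to the others, and a reader would follow it as written.

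Several stronger readings are tempting, and the document does not support them.

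- **That allocations are fixed in advance.** Minimisation has no preset list. Each assignment depends on the characteristics of those already allocated and of the next participant. The issue is predictability.
- **That consent or baseline testing could be steered.** Allocation already follows both, so this route is weak. For the same reason, asking for allocation to be released later would add nothing.
- **That the lead researcher knows every arm and keeps a tally.** Set-up and monitoring make knowledge of the arm plausible, but the article does not say so. Nor does it say who knows the factors or runs the minimisation.
- **That most allocations are certainly forced.** With one binary factor only half are.
- **That leaving the factors out of the model inflates the standard error.** The planned test is Group × Time in a mixed model. A factor with a constant effect on a person's scores largely cancels from within-person change, and the covariate list can be left to the analysis plan.

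**Conclusion.** The point holds in a limited form. As written, randomisation applies to 1 of 44 participants, and the other 43 are allocated by a method for which no random element is stated, in tension with the description of participants as randomised elsewhere in the article. If the text is followed literally, about half of the allocations are forced with one binary factor and roughly 70–85% with two to four. A fully informed observer would guess 75–92% of them correctly. These figures rest on the assumed number and balance of factors, equal weights and random tie-breaking.

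The realistic exposure is narrow: the order and timing of allocation around switch-on, and exclusion or withdrawal just before it. It depends on unblinded staff knowing the factors and past allocations, which is plausible at this site but not stated. The change is worth making because it is nearly free and, according to Trial status, recruitment had not begun.

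**What to change.** Reword Randomisation and blinding so that every participant, the first included, is allocated by minimisation with a random element: for example, the imbalance-reducing arm with probability 0.8, and 0.5 when the arms are tied. State that a computer program generates the allocation and that the lead researcher does not operate it. Bring Test procedure into line with the same description. If the full protocol already provides for this, the article's sentence only needs to say so.

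The cost is one program setting and an operator separate from the lead researcher. Balance loosens slightly: the mean final difference in group size goes from about 0.3–0.5 to about 1 participant. The sample size does not change. The random element does not remove predictability: a fully informed observer would still guess 69–77% correctly. But no allocation would then be certain, and keeping the lead researcher away from the program limits who could hold the information needed to guess.

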### Interventions

#### Auditory training

All participants will complete auditory training following the Adult Cochlear Implant Home-Based Auditory Training Manual – Post-lingual Hearing Loss [14]. Published by Cochlear®, the auditory training manual provides a series of activities of increasing difficulty. Listening activities range from ‘Module 1’ which involves daily practice of listening and identifying environmental sounds (e.g. kettle boiling, phone ringing) to ‘Module 16’ which involves partnered conversations where participants are required to repeat what is heard and most importantly, what is understood, during a conversation [14]. The auditory training manual also includes instructions for completing computer-based activities via the Angel Sound™ program [14]. Angel Sound™ is an adaptive auditory training program designed for CIRs and involves similar listening activities to those included in the training manual. Participants will be encouraged to use Angel Sound™ in conjunction with the training manual activities. Participants will be instructed to remove their contralateral hearing aid to ensure reliance upon and increased use of the cochlear implant during training.

#### Adaptive computerised cognitive training

The Brain HQ (Posit Science™) program will be used for adaptive CCT. Brain HQ is a commercially available auditory-cognitive training program and findings from our recent meta-analysis [17] suggest that Brain HQ (previously known as Brain Fitness) may improve cognition in adults with hearing loss. There is also high quality (i.e. Level 1) evidence in support of the efficacy of Brain HQ for improving cognition in older adults [32]. To determine whether CCT provides an additive therapeutic effect on study outcomes beyond the standardised auditory training regime, participants will only complete *visual* CCT activities that target cognitive domains (i.e. Gsm and EF) involved in the successful processing of sound and speech. CCT will therefore place no demand upon a participant’s hearing ability and will not interfere with the standardised post-implant auditory training rehabilitation protocol as recommended by each participant’s implant audiologist. In accordance with the CHC-M taxonomy of cognitive outcomes (Webb et al., 2018), Brain HQ CCT will involve the following activities designed to train each narrow cognitive ability within their corresponding broad domain: (1) ‘Juggle Factor’ will train high-WM within Gsm, (2) ‘Mind’s Eye’ will train low-WM within Gsm, (3) ‘Scene Crasher’ will train STM within Gsm, (4) ‘Card Shark’ will train updating within EF, (5) ‘Mind Bender’ will train shifting within EF, and (6) ‘Freeze Frame’ will train inhibition within EF. Participants will begin the training protocol on the least challenging level and the program will increase or decrease (i.e. adapt) task difficulty depending on participant progress during training. Participants will complete 20 min of CCT, 5 days a week for 12 weeks, totalling 20 h of CCT.

#### Non-adaptive computerised cognitive training

The same training protocol and Brain HQ exercises will be completed by participants in the non-adaptive CCT group to ensure intervention parameters (i.e. stimuli, length of training) are equal across groups. However, training exercises will be limited to the least challenging level (i.e. non-adaptive) to ensure no therapeutic benefit is experienced during training.

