**Results:**

The results of this trial will clarify whether the auditory training combined with cognitive training will improve cognition, sound and speech perception, mood, and quality of life outcomes in adult cochlear implant recipients.

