The current study will therefore examine whether combining auditory training with adaptive CCT will provide greater improvement in cognition, sound/speech perception, mood, and quality of life in adult cochlear implant recipients, when compared to auditory training combined with non-adaptive (i.e. placebo) CCT.

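### The randomised contrast isolates adaptive difficulty, but several sentences claim an effect of cognitive training itself, which holds only if the lowest-level control is inert

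*Protocol article*

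**What the plan says.** **The comparison.** The aim paragraph closing the Background asks "whether combining auditory training with adaptive CCT will provide greater improvement in cognition, sound/speech perception, mood, and quality of life" than auditory training with non-adaptive CCT. The Abstract (Methods), Methods/design and Data analysis sections give the same contrast.

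**The arms.** On the adaptive arm: "Participants will complete 20 min of CCT, 5 days a week for 12 weeks, totalling 20 h of CCT". Six visual exercises are used, one for each narrow cognitive ability measured as an outcome. On the starting point: "Participants will begin the training protocol on the least challenging level". On the control: "The same training protocol and Brain HQ exercises will be completed by participants in the non-adaptive CCT group", with stimuli and training length equal across groups. The difference is that control exercises are "limited to the least challenging level (i.e. non-adaptive) to ensure no therapeutic benefit is experienced during training". Neither arm receives auditory training without CCT.

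**The wider wording.** The section on adaptive CCT gives a purpose that does not mention adaptivity: "To determine whether CCT provides an additive therapeutic effect on study outcomes beyond the standardised auditory training regime". The Abstract (Results) says the trial "will clarify whether the auditory training combined with cognitive training will improve cognition" and other outcomes. Three more places read the same way. The Abstract (Background) frames the aim as whether home brain training helps memory and thinking. Test procedure says the 3-month follow-up will show lasting benefit of CCT. The Discussion speaks of determining whether auditory training with CCT improves cognition.

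**The concern.** The article carries two questions. One is whether adaptive difficulty helps, given the same exercises. The other is whether cognitive training helps, given auditory training. The trial randomises only the first. The two coincide if practice at the lowest level has exactly no effect, and the article presents that as something the design guarantees.

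What is at stake is the conclusion, above all after a null result. The Data analysis section adds Bayes factors because they can show that data favour the null hypothesis, so evidence for no difference is a planned, reportable finding. Combined with the wider wording, it could be taken to mean that CCT adds nothing to auditory rehabilitation, which does not follow if the control exercises themselves do some good. Likewise, a positive difference could be quoted as the whole benefit of CCT when it may be only part of it.

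**Working it through.** **1. Training time.** 20 min × 5 days × 12 weeks = 1,200 min = 20 h, as stated. By the matching statement in the control section, this applies to both arms.

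**2. What the contrast identifies.** Let *A* be the effect of adaptive CCT and *L* the effect of lowest-level CCT, each relative to auditory training alone.

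- Adaptive arm: auditory training + *A*
- Control arm: auditory training + *L*
- Randomised contrast: *A* − *L*

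The wider question concerns *A*. The contrast equals *A* only if *L* = 0. If *L* ≥ 0, then *A* − *L* ≤ *A*, so the contrast is a lower bound on *A*. If *L* were negative, it would overstate *A*.

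**3. Can the trial check *L* = 0?** No arm omits CCT, so no randomised comparison isolates *L*. The planned within-group time effects do not help: change in controls mixes implantation, auditory training, retesting and any effect of the exercises. The article cites nothing for *L* = 0, and Methods/design calls the comparator an active control.

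**4. Illustration of size.** Write *A* = *d* and *L* = *r* × *d*, so the contrast is (1 − *r*) × *d*. The article gives neither value. Assume *d* = 0.50 SD:

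| *r* (assumed) | Contrast |
|---|---|
| 0 | 0.50 SD |
| 0.25 | 0.75 × 0.50 = 0.375 SD |
| 0.50 | 0.50 × 0.50 = 0.25 SD |

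**5. Does the sample size depend on this?** The stated 36 reproduces for a group-by-time interaction with 2 groups, 3 time points, alpha .05 and Cohen's *f* = 0.25, assuming a correlation of 0.5 between repeated measures and sphericity (the article gives neither). The noncentrality is *f*² × *N* × 3 / (1 − 0.5) = 0.0625 × 36 × 3 / 0.5 = 13.5 on 2 and 68 degrees of freedom, and power is 0.906. (The article prints 0.25 as *f*²; 36 reproduces under these assumptions only with *f* = 0.25. That is a separate matter.)

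If 0.25 had been meant as adaptive CCT versus no CCT, the detectable *f* would be 0.25 × (1 − *r*):

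| *r* (assumed) | *f* | Power at 36 |
|---|---|---|
| 0 | 0.25 | 0.91 |
| 0.25 | 0.1875 | 0.67 |
| 0.50 | 0.125 | 0.34 |

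If it was meant as adaptive versus non-adaptive, nothing changes. The Power analysis section refers only to two intervention groups, so no sample-size error can be inferred.

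**The case against.** The strongest reply is that the stated question is the one the design answers. The formal aim, the design section and the sentence saying what the Bayes factors will be evidence of all name adaptive versus non-adaptive CCT. The additive phrase introduces the reason for using only visual exercises, and the Abstract's Results sentence directly follows a full statement of the comparison. The active control is a disclosed choice made for participant blinding, which an arm with auditory training alone would lose.

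Most of this stands, and it rules out several stronger readings that a reader might infer:

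- *The trial cannot answer its stated question.* It can answer the formal aim, and a positive contrast would also support an added benefit of CCT if the control effect is not negative.
- *The control is a smaller dose of treatment.* Time and stimuli are equal; only difficulty is lower.
- *The plan directs that a null be reported as CCT adding nothing.* No sentence says so; the risk comes from the wider wording.
- *The trial is underpowered for this reason.* That depends on which contrast the planning effect represents, and the article does not say.

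What the reply does not remove is the guarantee in the control section. Nor does it explain the wider wording as one loose phrase, since it appears in five places.

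**Conclusion.** The concern holds as a mismatch between the contrast and some of the claims made for it. The randomised comparison identifies the effect of adaptive difficulty over the same exercises held at the lowest level, both with auditory training. Statements about CCT itself need the further assumption that the control is inert, which the article asserts and cannot test.

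In practice, a positive difference supports added benefit as a lower bound, provided the control effect is zero or positive. A null result, including a Bayes factor favouring the null hypothesis, says nothing definite about CCT versus no CCT, and the size of the difference is not the size of the CCT effect. How far the two could differ is unknown: the 0.50, 0.375 and 0.25 SD figures rest on assumed values and are illustrative only. This is a correction to wording and permitted conclusions, not a defect in the comparison, analysis or sample size.

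**What to change.** - In the Abstract (Background and Results), Test procedure, Adaptive computerised cognitive training and Discussion, word the question and conclusion as in the aim paragraph: adaptive versus non-adaptive CCT, both with auditory training.
- In Non-adaptive computerised cognitive training, replace the guarantee of no benefit with a stated assumption that lowest-level practice has little or no effect, and acknowledge that the trial cannot verify it.
- In Data analysis and statistical methods, state in advance that a null between-arm result, by p value or Bayes factor, will not be read as evidence that CCT adds nothing to auditory training.

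The cost is text only, and Trial status says recruitment had not begun. The downside is a narrower claim. If the sponsor wants to keep the wider claim without the assumption, it would need a comparator with auditory training alone, at the expense of the blinding that the present control provides.
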